**6. DESCRIPTION OF EXPOSURE**

*See point 4.2. above.*

**7. Safety evaluation:**

**7.1. Description of safety evaluation parameters**

The sole constraints placed on subjects participating in this study are with respect to the salivary cortisol assays which will be taken using a swab, i.e. a small cotton bud subjects will have to chew on to thoroughly soak through with saliva (see Annex 1).

Within the framework of this study the only foreseeable risks are those connected to the use of the swabs, namely an intolerance to the strain of cotton used or misuse of the swab.

**7.2. Planned methods and timetable to be used in terms of measuring, collecting and analysing safety evaluation parameters**

Subjects participating in the study shall be interviewed regarding the risks listed above in section 7.1.

**7.3. Procedures in place for the recording and reporting of adverse events**

**7.3.1. Definitions**

An **adverse event** refers to a harmful event affecting a person undergoing biomedical research regardless of whether said event is related to research, the product being researched or any other factor.

An **adverse effect** refers to a harmful, undesirable reaction related to the experimental drug being taken which occurs after taking said drug at the dosage normally recommended for humans.

A **serious adverse event or effect (SAE)** is an event or effect which may contribute to the patient's death, endangerment of their life, the hospitalisation of the patient or extended hospitalisation, a significant or lasting disability or an event of effect which leads to a birth defect.

**The list of expected adverse effects** related to this study has been drawn up using the reference document.

An SAE is deemed to be unexpected (unexpected SAE) whenever it is not included in this list.

**A new discovery** may be: the unexpected frequency of an unexpected SAE, severe adverse events related to study procedures, insufficient effectiveness in treating life-threatening diseases and/or non-clinical data.

**7.3.2. Reference document to be used to define the unexpected nature of an SAE**

*Not applicable within the framework of this study*

**7.3.3. List of expected adverse events**

*Not applicable within the framework of this study*

**7.3.4. Communication of SAEs and new discoveries**

As soon as an investigator is made aware of an SAE or new discovery, he/she should let the promoter of the study know by faxing him/her the SAE declaration form.

- If the SAE is unexpected or if notification is for a new discovery, the promoter should contact the investigator for the purposes of preparing an initial report which will be sent to the ANSM, the IRB and the principal investigator within 7 days in the event of a death. For instances of endangerment of the patient's life this timeframe shall be extended to 15 days.

When the event has not been resolved by the date the fax is sent, the investigator shall be under obligation to send an additional report for the purposes of documenting the patient's progress or provide an update on missing data.

- For expected serious adverse events all files shall be compiled by the promoter when drafting annual safety reports.

**7.3.5. Notification of non-serious adverse events**

These should be briefly described by the investigator in the summary sheet included for this purpose in the case report form.

**7.4. Monitoring procedures and timescales following the appearance of an adverse event**

Whenever a serious adverse event persists, including after the end of the study, the investigator shall continue monitoring the patient until the event is deemed to have been resolved and shall then provide the promoter with all data collected during monitoring.

**7.5. Specific research committees (may vary based on the protocol)**

**Steering committee**

This committee shall be made up of the clinician initiators of the project, the biostatistician responsible for the project and promoter representatives.

This committee shall define the general organisation and procedural methods for research and co-ordinate all information.

It shall be responsible for initially determining the methodology to be used and shall decide, over the course of research, what steps to take in the event of unforeseen circumstances and oversee research progress, particularly in terms of tolerance and adverse events.

**7.6. Safety reports**

- Annual safety reports: the promoter shall draft annual safety reports and send these to the ANSM, the IRB and the principal investigator. The principal investigator shall provide the promoter with all data required to prepare this report.
- Final report: this report shall be prepared by the promoter and principal investigator within one year of the end of the study. All investigators shall be notified of study results. A summary shall be sent to the ANSM by the promoter.

**8. Statistics**

**8.1. Description of anticipated statistical methods to be used, including a timetable for any anticipated interim analyses**

**Description of sampling**: qualitative variables shall be described as a percentage, using the absolute frequency and a 95% confidence interval, with quantitative variables being described as an average and standard deviation or as medians over a range and with interquartile intervals.

**Description of biological stress**: this shall be described by calculating the difference between cortisol peak(s) observed and cortisol levels measured on the day off (as an average and standard deviation or as medians over a range and with interquartile intervals).

**Description of perceived stress**: the ASA score shall be described as a median and standard deviation.

**For exploratory purposes**: a comparison of the delta peak/cortisol base rate from the three ARM posts using a non-parametric Kruskal Wallis test, with the same being carried out based on ARM seniority, the seriousness of the call and the doctor's status (emergency doctor or independent practitioner); a comparison of the delta peak/cortisol base rate per chronic stress levels (PNOSI questionnaire) and personality (NEO PI-R questionnaire).

The ASA score (perceived stress) shall be compared to the delta peak/cortisol base rate (biological stress) using the Spearmann correlation coefficient.

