**4. Research design**

This was a controlled physiological study carried out in healthy human beings, with each subject acting as their own witness.

Four experimental conditions were used for ARMs whilst two experimental conditions were used for emergency care doctors and private practitioners.

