**4.2.1. CHR METZ-THIONVILLE Centre 15 organisational structural and experimental conditions being assessed**

ARMs work 12-hours shifts every night with rotation happening every two hours, followed by three days off for a total of 36 hours a week.

Emergency doctors also work 12 hour shifts for a total of 48 hours a week, however they rotate between the medicine department, dispatch and SMUR/resuscitation.

Private practitioners more often than not work shifts of 12 hours.

The operational structure of Metz Centre 15 is as follows: medical dispatch assistants (ARMs) are assigned to one of three areas:

- **Call ARMs** provide the first line of support, answering all incoming calls. They assess the severity of the situation at hand and, based on this information, transfer the call to either an emergency doctor or a general practitioner. This position is the most stressful of the three.

- **Action ARMs** provide various means of intervention. This area organises patient transport and is responsible for ringing up ambulances, the fire brigade or SMUR teams based on what is required for the matter at hand. They only act once they have received due instruction from either a general practitioner or emergency doctor.

- **Assessment ARMs** are in charge of collecting reports from the various dispatch assignments.

The way the doctors work however is quite different. Call ARMS send independent practitioners (who are more often than not general practitioners) less serious calls which still require medical advice or just an ambulance. Emergency doctors manage the more severe situations which require more in the way of support; they are the only ones who can authorise an SMUR dispatch, as an example.

This study will be conducted by including the same number of experienced ARMs (i.e. those with over five years of experience) as younger ARMs (i.e. those with less than five years' experience). The same dispatch assistant will also be studied whilst working in each of the three areas.

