***Experimental conditions***

Salivary cortisol will be collected for each ARM over three working days in three different positions: calls, resource deployment or action, and assessment.

Participants will be notified of proper sampling conditions for the salivary cortisol assay. Once enrolled on the study participants shall undertake not to drink or eat anything for half an hour prior to the sample being collected as well as during the two hours when samples are taken. Subjects must also agree not to smoke thirty minutes prior to samples being taken as well as during the sample collection period. Regarding other variation factors which affect salivary cortisol levels, light levels will not vary over the working day and subjects will be working in a seated position, so standing will not be accounted for.

Calls assays will be taken for will be for the same time period to prevent any bias arising in terms of inter- and intra-individual circadian variations in salivary cortisol levels.

The first incoming call for the ARM shall be used as the reference, however accidental or mistaken calls will be excluded from the study. During the call, a salivary control assay will be taken for the call ARM, with the first assay being marked T0. Additional assays will be conducted for call ARMs every 15 minutes after T0 for 1 hour and 30 minutes, followed by a final assay at two hours after the call, which translates to eight assays which will be used to generate the acute stress curve. Cortisol assays will all be carried out at the same time to prevent nycthemeral variations. Each sample will be taken as soon as the subject ends the call and hangs up the phone.

The same salivary cortisol assay following the same principle will then be carried out on the doctor the call was transferred to. The same assay will also be carried out on the action ARM and the assessment ARM. The next day the salivary cortisol assay will be carried out on the same ARMs but as assigned to different areas.

Three medical dispatch assistants should therefore have salivary cortisol assays administered every day as should a doctor - either an emergency doctor or independent practitioner - based on the severity of the call.

Each additional call will be noted when taking salivary cortisol measurements. Each event over the two hour sampling period will likewise be recorded to prevent any bias arising and for a better understanding and analysis of the curves generated.

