## 4.3. Description of measures taken to reduce and prevent biases from arising, more specifically for the purposes of ensuring random draws and blinding methods

This study will be conduct openly and does not require a random draw.

Each subject will be their own witness. Subjects will be assessed under identical experimental conditions which are specific to their position (ARMs and medical personnel).

See point 4.2. for more information in this regard.

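### Section 8.1 compares the three ARM posts with Kruskal-Wallis, a test for independent groups, although the same ARMs are measured in all three posts; the unit of analysis for seniority is left open

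*Protocol*

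**What the plan says.** **The test.** Section 8.1, in its exploratory part, plans "a comparison of the delta peak/cortisol base rate from the three ARM posts using a non-parametric Kruskal Wallis test". It then extends the test to other factors, "with the same being carried out based on ARM seniority" being the first. The quantity compared is built from "the difference between cortisol peak(s) observed and cortisol levels measured on the day off".

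**The design.** Section 4.2.1 states: "The same dispatch assistant will also be studied whilst working in each of the three areas". The experimental conditions in section 4.2.2 repeat it: "Salivary cortisol will be collected for each ARM over three working days in three different positions". Section 4.4 gives each ARM four sampling sessions of eight samples. These are the three posts plus one day off, so a single reference day serves all three of an ARM's deltas.

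**Status and size.** Section 8.2 expects 20 ARMs and calls the main objective descriptive. Section 8.3 labels the tests exploratory, at an alpha of 5%. Section 3.2 lists as its first secondary objective a comparison of ARM stress between shifts, which in context means the posts. Section 4.2.1 asks for equal numbers of ARMs above and below five years of experience.

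**The concern.** Kruskal-Wallis compares samples from different people. Here the three samples come from the same people. If some ARMs have generally higher deltas than others, that difference is common to the three posts and should drop out of the comparison. Kruskal-Wallis leaves it in the yardstick against which the posts are judged. The test then rejects too rarely when there is no difference, and too rarely when there is one.

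This is not a detail left to a later analysis plan. The protocol names the test, and the test does not fit the protocol's own design. It is the only test in section 8.1 that compares the posts. Section 8.2 also says the study may serve as a feasibility study for the comparative objectives, so a real post difference that is missed here could misdirect a later study.

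Seniority raises a separate question. It is a property of the person, and each ARM has up to three deltas. Section 8.1 reuses the same test without saying whether the unit is the ARM or the delta.

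**Working it through.** **Inputs.** From the protocol: 20 ARMs, three posts, equal seniority groups (so 10 against 10), alpha 5%. Not in the protocol, hence assumed: the correlation ρ between two deltas of the same ARM (ICC), taken from 0 to 0.7; the effect, one post shifted by 0.5 total SD; normal data with equal correlation between posts. The protocol gives no power or effect size, so there is no figure of its own to reproduce.

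**Step 1: is ρ likely to be zero?** Write an ARM's delta in post j as peak_j − B, where B is that ARM's day-off level. Suppose stable differences between people cancel in the subtraction. The error in B still enters all three deltas, so ρ = Var(B) / [Var(B) + Var(peak)].
- Equal occasion variances: ρ = 1 / (1 + 1) = 0.5.
- B as the mean of the eight day-off samples with independent errors: ρ = (1/8) / (1/8 + 1) = 1/9, about 0.11.
- If ARMs differ in how strongly they react, ρ is higher than these values.

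Both figures rest on assumed variances. They show only that zero is not the natural default.

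**Step 2: type I error for posts, by approximation.** With equal correlation, the true variance of a difference between post means is (1 − ρ) times the variance under independence. The Kruskal-Wallis statistic then behaves roughly like (1 − ρ) times a chi-square with 2 degrees of freedom, whose 5% critical value is 5.991. The true alpha is about exp[−5.991 / (2(1 − ρ))]:
- ρ = 0: exp(−2.996) = 5.0%
- ρ = 0.1: exp(−3.328) = 3.6%
- ρ = 0.3: exp(−4.279) = 1.4%
- ρ = 0.5: exp(−5.991) = 0.25%
- ρ = 0.7: exp(−9.985) = 0.005%

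**Step 3: simulation for posts (20 ARMs, 3,000 runs per value of ρ).**

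| Assumed ρ | Kruskal-Wallis type I error | Kruskal-Wallis power, 0.5 SD | Friedman power, 0.5 SD |
|---|---|---|---|
| 0 | 5.2% | 32% | 26% |
| 0.1 | 3.2% | 30% | 28% |
| 0.3 | 1.4% | 27% | 35% |
| 0.5 | 0.3% | 21% | 47% |
| 0.7 | 0.0% | 16% | 69% |

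The simulated type I errors agree with step 2. A separate run of 4,000 gave Friedman type I errors of 5.4 / 5.1 / 5.8 / 4.7% at ρ = 0 / 0.3 / 0.5 / 0.7, so the matched test holds its level.

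**Step 4: seniority, if all 60 deltas were pooled.** With three deltas per ARM the design effect is 1 + 2ρ, the effective sample size is 60 / (1 + 2ρ), and the true alpha is about 2[1 − Φ(1.96 / √(1 + 2ρ))].

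| Assumed ρ | Design effect | Effective n | True alpha |
|---|---|---|---|
| 0.1 | 1.2 | 50 | 7.4% |
| 0.3 | 1.6 | 37.5 | 12.1% |
| 0.5 | 2.0 | 30 | 16.6% |
| 0.7 | 2.4 | 25 | 20.6% |

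Simulation (4,000 runs) gave 11.8 / 15.5 / 21.1% at ρ = 0.3 / 0.5 / 0.7. One mean per ARM gave 4.9 / 4.3 / 5.4%.

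**The case against.** **The tests are exploratory.** Sections 8.1 to 8.3 say so, and the main objective is descriptive. No sample size, stopping rule or main conclusion depends on this comparison. For posts the error is conservative, so it produces no false claims. All of this stands and limits the seriousness. It does not make an independent-groups test fit repeated measurements.

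**The loss depends on a correlation nobody has stated.** This also stands. At ρ = 0 Kruskal-Wallis is valid and has more power (32% against 26%), and at 0.1 it is still marginally ahead. Hence the range is shown from zero.

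**Own control.** A reader might infer from "with each subject acting as their own witness" that the test throws away most of the benefit of using each person as own control. The protocol does not support that. Section 4.1 lists the witness as a separate condition beside the posts, doctors have a witness condition with only one work condition, and section 4.2.2 makes the day off the source of reference values. The delta already contains that own-control comparison. What is lost is the further pairing between posts.

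**Seniority.** A reader might also infer that the seniority test will count each ARM three times. The text does not say this. Comparing within one post, or using one value per ARM, would be equally consistent with it and would keep the error near 5%. The supportable point is that the unit is not fixed, although the same sentence does fix the test.

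**Conclusion.** The mismatch is confirmed from the protocol's own text: section 8.1 names an independent-groups test for posts in which, by section 4.2.1, the same ARMs are all measured. Under the assumed correlations the test falls below its nominal 5% as soon as the deltas are correlated (about 1.4% at 0.3 and 0.3% at 0.5). From about 0.3 upwards it loses material power: 27% against 35% at 0.3, and 21% against 47% at 0.5. These sizes rest on normal data, equal correlation between posts, a shift of 0.5 SD in one post and complete data from 20 ARMs.

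It should be fixed because it concerns the first secondary objective. It does not threaten the study: the descriptive main objective is unaffected. For seniority the finding is an open unit of analysis, with roughly 7 to 21% false positives if the open choice were settled by pooling and the correlation lay between 0.1 and 0.7.

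**What to change.** In section 8.1:
- **Posts.** Replace Kruskal-Wallis with the Friedman test, with paired Wilcoxon tests as follow-up. If some ARMs lack a post, which is possible because section 8.5 does not fill in missing data, use a mixed model with post as fixed effect and ARM as random effect. Fit it to the untransformed or rank-transformed delta. A log transformation is unsuitable because a difference can be zero or negative.
- **Seniority.** State one value per ARM, for example the mean of its deltas, compared by a rank-sum test.
- **Call severity.** Do not add it to the post model as a common covariate. Section 4.2.4 grades calls on different scales by role (P0 to P2, B0 to B2, R1 to R4).

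One limit remains. Section 4.2.1 has the call, action and assessment ARMs sampled on the same call, so values are also grouped by call. A random ARM effect alone does not cover this, and the report should say so.

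The cost is one paragraph and no new data.

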**3.2. Secondary objectives:**

- Compare levels of both perceived and biological stress in ARMs amongst the various shifts

- Study the difficulty of the tasks required of the various ARM shifts

- Study the correlation between perceived and biological stress

- Study the correlation between the severity of the situation being dealt with over the phone and stress

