**4.2.4 Other data collected**

Intervening events (such as other calls, specific contexts, etc.) shall be recorded during periods where salivary cortisol assays are being taken (i.e. over 2 hours per each subject).

Furthermore during each call, the gravity of the situation at hand will be assessed using the following classification to look for a correlation between physiological stress levels and the seriousness of the call.

For ARMs:

Three levels of priority shall be applied when transferring the call to a dispatch doctor:

P0: procedural response of an SMUR team being sent followed by priority dispatch

P1: priority dispatch

P2: dispatch that can be put on hold without risk to the patient until other dispatches which are currently out can arrive

For dispatch doctors:

Dispatch doctors make their decisions based on four levels of emergency:

R1: a patent or latent life-threatening emergency requiring a resuscitation team (SMUR) being dispatched.

R2: a real emergency although not life-threatening which would require the attention of a nearby doctor, ambulance or the fire brigade within a period of time contractually agreed to between the dispatcher, the acting party and the caller.

R3: access to continuous care required although the time it takes to do so presents no immediate risk; a medical prescription for later may be suggested.

R4: medical advice or drug prescription can be provided over the phone.

For assessment ARMs:

Three levels of priority are applied by ARMs when forwarding assessments to dispatch doctors:

B0: assessment with signs of distress which were not apparent during the call. This call should be answered as a priority by the emergency dispatch doctor.

B1: assessment providing additional information which was not present during the initial dispatch but absent of any signs of distress or seriousness.

B2: an assessment in line with the data collected during the call to dispatch.

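### The severity objective asks for a correlation on ordered levels, but section 8.1 analyses call severity with Kruskal-Wallis, which ignores the order and gives neither coefficient nor direction

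*Protocol*

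**What the plan says.** Three parts of the protocol bear on this.

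- **Objective.** Section 3.2 lists as a secondary objective: "Study the correlation between the severity of the situation being dealt with over the phone and stress". Section 4.2.4 gives the same reason for grading each call: "to look for a correlation between physiological stress levels and the seriousness of the call".
- **Severity scales.** Section 4.2.4 grades severity from most to least urgent. For ARMs (P0-P2): "Three levels of priority shall be applied when transferring the call to a dispatch doctor". For doctors (R1-R4): "Dispatch doctors make their decisions based on four levels of emergency". For assessment ARMs (B0-B2): "Three levels of priority are applied by ARMs when forwarding assessments to dispatch doctors".
- **Analysis.** Section 8.1 compares the cortisol delta between the three ARM posts "using a non-parametric Kruskal Wallis test" and extends that test to severity: "with the same being carried out based on ARM seniority, the seriousness of the call". A rank correlation is named once, for the ASA score against the cortisol delta: "using the Spearmann correlation coefficient".

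Section 8.2 expects 20 ARMs and 20 doctors. It calls the main objective descriptive and says the study may serve as a feasibility study for the comparative objectives. Section 8.3 makes all tests exploratory at 5%.

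**The concern.** A correlation on an ordered scale asks whether stress rises or falls as severity rises, and by how much. Kruskal-Wallis asks whether at least one level differs from another. It suits the ARM posts, which have no natural order, but severity levels do have one.

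Three things are at stake:

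- The reported result would be a p-value without the coefficient or direction that the objective calls for.
- A steady gradient would be harder to detect, because four levels cost 3 degrees of freedom where a trend costs 1.
- A significant result could be reported as a correlation although the pattern is not monotone.

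This is not a detail left to a later analysis plan. The protocol names the test for severity, and in the same section it names a suitable method for its other correlation question.

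**Working it through.** **Step 1. What the test can see.** With N subjects, n_j of them at level j, and rank sum R_j at that level,

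H = [12 / (N(N+1))] × Σ R_j² / n_j − 3(N+1), referred to chi-square on k − 1 degrees of freedom.

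The sum is unchanged if the level labels are permuted. Swapping R1 with R3 gives the same H and the same p-value, so order cannot enter and no sign results. Spearman's coefficient r uses the order, has a sign, and is tested with t = r × √[(N − 2)/(1 − r²)]. This step needs no assumption and is enough to establish the mismatch.

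**Step 2. Inputs for the size of the loss.**

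- From the protocol: 20 doctors (8.2); one call condition and one witness condition per doctor (4.1), hence 20 call deltas; four levels for doctors and three for ARMs (4.2.4); alpha 5% (8.3).
- Not in the protocol, so assumed: two-sided testing, normal deltas with SD 1, the step in mean delta per severity level, the spread of calls over levels, and whether Kruskal-Wallis uses the chi-square or an exact cut-off.

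The protocol states no power, so there is no figure of its own to reproduce.

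**Step 3. Linear trend, 20 doctors split 5/5/5/5, chi-square cut-off** (simulation, 40,000 runs per row):

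| Step per level (SD) | Kruskal-Wallis | Spearman | Loss (points) |
|---|---|---|---|
| 0.2 | 8% | 15% | 7 |
| 0.4 | 23% | 45% | 22 |
| 0.5 | 36% | 63% | 26.5 |
| 0.6 | 52% | 78% | 26 |
| 0.8 | 79% | 95% | 16 |
| 1.0 | 95% | 99.5% | 5 |

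**Step 4. Vary the assumptions, still with a linear trend.**

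- Unequal four-level splits (2/6/7/5 and 2/4/6/8): loss 6 to 31 points.
- Exact 5% cut-off for Kruskal-Wallis, four levels: loss about 4 to 22 points. Part of the loss in the table therefore comes from the conservative chi-square cut-off and not from ignoring order.
- One doctor level empty (4/8/8): loss 3 to 16 points.
- ARMs on three levels, n = 20 (7/7/6 or 3/7/10): loss about 3 to 16 points.

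**Step 5. Other patterns.**

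- Only the most severe level raised by 1.5 SD: loss of −1 to +2 points with four levels occupied. With 4/8/8, Kruskal-Wallis is better by 15 points (50% against 35%).
- Three levels 7/7/6 with means 1, 1.5 and 0: Kruskal-Wallis 54%, Spearman 26%.
- Middle two of four levels raised by 1 SD (5/5/5/5, zero rank correlation): Kruskal-Wallis rejects in 30% of runs, Spearman in 3%.
- Symmetric U shape (5/5/5/5, zero rank correlation): Kruskal-Wallis rejects in 63% (±0.75 SD) to 90% (±1 SD) of runs, Spearman in about 1% or fewer.
- No difference between levels (5/5/5/5): Kruskal-Wallis about 4% with the chi-square cut-off, Spearman about 5%.

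**The case against.** The strongest defence is that a monotone gradient is itself an assumption. P0 triggers a procedural response in which a team is sent, and nothing in the protocol says that this is more stressful for the ARM than P1. With the shape unknown, an omnibus test in an exploratory analysis is a defensible choice, and for some patterns it is the more powerful one. No sample size or confirmatory conclusion rests on it, and section 8.2 calls the secondary objectives comparative.

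Most of this stands as a limit on the consequences. It does not remove the mismatch: sections 3.2 and 4.2.4 say correlation, and an omnibus p-value is not one. Per-level medians would show a non-monotone pattern without giving up the coefficient.

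Two stronger readings are tempting but unsupported.

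- A reader might infer a fixed power loss of 25 points or more. That size appears only near the peak of the range, with linear steps of about 0.5 to 0.6 SD in a balanced split (about 0.5 to 0.8 SD in unequal ones) and the chi-square cut-off. The protocol gives none of these.
- A reader might infer inflated false positives. When Kruskal-Wallis rejects under a U shape, the levels truly differ and the test is right to say so. It holds its size when nothing differs.

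**Conclusion.** The mismatch holds and depends on no simulated figure: the stated objective is a correlation on ordered levels, and the named test cannot produce one. Any power loss is conditional. With 20 doctors over four occupied levels, a linear trend and normal data, it is roughly 4 to 31 points, depending on step size, call split and cut-off. With three levels it reaches about 16 points. It is about zero, or reversed, if only one level differs or the pattern is not monotone. A significant Kruskal-Wallis result would show that levels differ, not that stress is correlated with severity. Because the analysis is secondary and exploratory, the priority is minor to moderate.

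**What to change.** In section 8.1, take call seriousness out of the Kruskal-Wallis list and add the following:

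- Estimate the Spearman coefficient, with a 95% confidence interval, between the ordered severity level and the cortisol delta. Do the same for the ASA score, because section 3.2 speaks of stress and the study measures it both ways.
- Do this separately by staff group, post and scale: P for call ARMs, P for action ARMs on the same call, B for assessment ARMs, R for doctors. Each ARM is studied in all three posts (4.2.1), so working within a post keeps one observation per person.
- Show the doctor coefficient also by doctor type. Sections 2.5.3 and 4.2.1 route calls by severity to emergency doctors or general practitioners, so a pooled coefficient mixes severity with type of doctor.
- Keep medians and interquartile ranges per level to show non-monotone patterns.

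A Jonckheere-Terpstra test could be added as a trend test, but it does not itself give a correlation coefficient and so cannot replace Spearman here.

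The cost is a short rewording, with no new data or subjects. The downside is little power against non-monotone patterns. The intervals will be wide: by the usual Fisher approximation with n = 20 and a coefficient near zero, the half-width is tanh(1.96/√17) = tanh(0.475) ≈ 0.44, and wider still within doctor type. For a study that may inform a later one, that is still more useful than an omnibus p-value.
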